## Abstract

**Study protocol registration:**

Preregistration can be found here: https://osf.io/3rhk4/overview.

## Introduction

1

### Problem statement and theoretical background

1.1

Mental disorders are increasing globally and constitute one of the most pressing health challenges of modern society (WHO, 2019). Mental health, understood as the capacity to cope with stressors, realize one’s abilities, and participate productively in society, is increasingly threatened by chronic psychosocial strain (WHO, 2019). Despite the availability of effective psychotherapeutic treatments, mental health care systems remain under-resourced, and stigma continues to prevent many individuals from seeking help, sustaining persistent treatment gaps (WHO, 2019). European data underscores the magnitude of this problem. In recent surveys, nearly half of respondents reported emotional or psychosocial problems such as anxiety or depression, yet a substantial proportion did not receive professional support (European Commission, 2023). Young people appear particularly affected, reporting high levels of unmet mental health needs and marked increases in depressive symptoms during recent crises (European Commission, 2022). These developments highlight the need for interventions that are effective, scalable, and acceptable across clinical and non-clinical settings.

### The role of mind–body interventions in mental health care

1.2

A key response to these challenges has been the growing integration of mind–body medicine (MBM) approaches that intentionally target both psychological and physiological regulation (Luberto et al., 2020; Solanki et al., 2023). MBM includes a broad set of techniques—such as mindfulness, relaxation training, guided imagery, biofeedback, yoga, and breathing-based interventions—that aim to reduce stress, improve self-regulation, and enhance quality of life with low implementation barriers and minimal side effects (Solanki et al., 2023). This mind–body perspective explicitly challenges traditional separations of “mental” versus “physical” health and emphasizes their reciprocal, dynamic interaction (Luberto et al., 2020). Such a perspective is particularly relevant given that prolonged stress without sufficient recovery contributes to dysregulation and increases risk for chronic conditions, including anxiety and depressive disorders (Schulz et al., 2023).

However, the widespread use of mind–body techniques contrast with a persistent scientific limitation: interventions are often used as interchangeable tools for “relaxation” despite conceptual differences and substantial variability in individual responsiveness (Luberto et al., 2020; Solanki et al., 2023). This is clinically consequential. If different techniques engage distinct regulatory pathways, then selecting the right tool may matter and may differ across individuals and clinical profiles.

### From stress physiology to mechanistic targets

1.3

Stress and recovery are reflected in coordinated changes of the autonomic nervous system (ANS). The sympathetic branch supports acute mobilization, while parasympathetic activity supports recovery and restoration (Christensen et al., 2020). Beyond acute adaptation, chronic activation without adequate recovery can contribute to allostatic load, a cumulative biological burden linked to a wide range of mental and physical health outcomes (McEwen, 2002).

This study focuses on regulation as a measurable psychophysiological process and integrates brain, heart, and respiration data, with speech measures included as an optional extension. Importantly, physiological change is not always consciously perceived. Subjective experience and autonomic markers can diverge, highlighting the need to jointly assess subjective and objective indices of regulation (Mehling et al., 2018).

### Mindfulness versus relaxation: similar outcomes, distinct regulatory strategies

1.4

Among MBM approaches, mindfulness and relaxation-based techniques are particularly prominent in clinical psychology and psychotherapy. Mindfulness is typically defined as present-moment, nonjudgmental awareness of internal experience (Kabat-Zinn, 2008) and is cultivated through exercises such as breath observation and body scan practices (Cayoun et al., 2018).

In contrast, relaxation techniques aim more directly at downregulating arousal and eliciting a measurable relaxation response (Pearson et al., 2015). A highly accessible relaxation format is guided imagery, which uses imagination and memory to evoke calming sensory experiences and promote affect regulation (Pearson et al., 2015). Clinically, safe place imagery is frequently used to support emotional safety and distress tolerance, particularly in trauma and anxiety contexts (Pearson et al., 2012, 2015).

Although both approaches are often implemented to reduce stress and arousal, they should not be mechanistically identical. Relaxation primarily targets physiological downregulation, while mindfulness emphasizes attentional and metacognitive regulation (Luberto et al., 2020). This distinction motivates a key premise of the study: similar subjective outcomes may be supported by different neurophysiological pathways, which may matter for personalization and clinical translation.

### The missing link: brain–body interaction as a mechanistic framework

1.5

A central limitation in current evidence is that physiological indices are frequently analyzed without capturing the fast neural dynamics that initiate and shape autonomic regulation. Regulatory processes unfold over time and may rely on brain–body feedback loops rather than one-directional control. Visceral signals can shape brain dynamics and cognition, suggesting that regulation should be conceptualized as an interaction between central and peripheral processes rather than separate outcome layers (Azzalini et al., 2019).

Accordingly, this study adopts brain–body coupling as a mechanistic core. Regulation is examined not only as changes in cardiac activity or respiration and changes in neural activity, but as dynamic coordination between neural oscillations and physiological rhythms. Multimodal neuroscience methods are therefore necessary. MEG provides millisecond temporal resolution suitable for capturing rapid neural dynamics during brief interventions. The study integrates MEG with ECG and respiration to examine whether mindfulness and relaxation induce distinct neural signatures and whether these signatures couple differently to cardiac and respiratory rhythms across stress, intervention, and control contexts.

### Why speech matters for neuroscience-based psychotherapy

1.6

Psychotherapy is fundamentally language-based. Verbal communication is not only a medium through which therapeutic interventions are delivered, but also a channel through which individuals express, organize, and reflect on internal states. In the present paradigm, spoken language is also the common delivery format of all auditory conditions. The body scan, safe place imagery, and podcast control condition are all presented as spoken audio, which means that neural responses to heard speech are an inherent part of the experimental setting. Because MEG can capture neural dynamics related to auditory speech processing with high temporal precision, speech-related neural tracking provides a relevant stimulus-engagement measure within this design. In the context of mind–body interventions, speech may provide an additional window into how participants process regulatory instructions and describe their subjective experience after regulation. At the same time, speech-related measures are methodologically challenging in MEG because overt speech can introduce movement and muscle artifacts. For this reason, speech is included in the present protocol as a complementary and carefully constrained extension of the main brain–body paradigm, rather than as the central focus of the study (Abbasi et al., 2021; Sanders, 2010). Because the podcast condition primarily requires sustained engagement with externally presented speech, whereas the body scan and safe place imagery conditions use speech to guide internally oriented regulatory processes, TRF-based neural speech tracking is expected to provide an index of stimulus engagement that may be strongest in the podcast condition.

### Rationale and positioning of the present study protocol

1.7

Despite the widespread use of mindfulness- and relaxation-based interventions, a key limitation in the current literature is the lack of time-resolved, multimodal investigations that directly compare these approaches within the same individuals. In particular, it remains unclear how these practices shape regulation across neural dynamics, autonomic physiology, and subjective experience in individuals with mental health conditions, and how these processes are coordinated over time within a brain–body framework.

This study protocol is designed to address this gap by investigating the mechanisms of brief mind–body interventions in clinically relevant populations using a standardized, multimodal experimental paradigm. Addressing this gap is important for strengthening the mechanistic basis of psychotherapy research and for informing the future development of mechanism-informed applications of mind–body interventions.

The protocol builds on the premise that regulation is best conceptualized as a dynamic brain–body process, rather than isolated changes in subjective experience or peripheral physiology. By integrating MEG with cardiac and respiratory measures, the study aims to characterize condition-related neural signatures and their coordination with autonomic rhythms during stress, regulation, and control contexts. In addition, the study incorporates repeated subjective ratings to capture experiential regulation over time. Speech-related measures are included as an exploratory extension to enhance psychotherapy relevance while accounting for methodological constraints in MEG.

Overall, the protocol adopts a mechanistic research strategy with three complementary aims: (1) to characterize acute regulation during brief mindfulness and relaxation interventions in clinical populations, (2) to examine brain–body coupling as a dynamic marker linking neural and autonomic processes, and (3) to explore sources of interindividual variability that may inform future personalization. In doing so, the study protocol provides a transparent and reproducible foundation for subsequent translational research on mind–body interventions in mental health care.

In addition to the clinical samples targeted in this protocol phase, the preregistered NeuroPsychth program (OSF: 10.17605/OSF. IO/3RHK4) includes a healthy reference cohort assessed with the identical paradigm to provide normative benchmarks for interpreting clinical patterns; no results from any cohort are reported in this manuscript.

## Aims, research questions, and hypotheses

2

This study aims to strengthen psychotherapy research by moving beyond outcome-focused evaluations toward a mechanistic understanding of brief mind–body interventions in clinically relevant populations, here in individuals with adult attention-deficit / hyperactivity disorder (ADHD) and depression. The long-term goal is to support the development of more differentiated, mechanism-informed, and potentially personalized applications of mindfulness- and relaxation-based interventions. The study examines how mindfulness-based and relaxation-based practices shape regulation across neural activity (MEG), autonomic physiology (cardiac activity and respiration), and subjective experience, with a particular focus on how these levels relate to each other over time. An exploratory speech component is included to increase psychotherapy relevance. Across aims, research questions, and hypotheses, analyses will first be conducted in the overall clinical sample. Where data quality and sample size permit, subgroup analyses will then be conducted within the adult ADHD and depression groups separately, and exploratory group comparisons between ADHD and depression will be examined to characterize potential clinical heterogeneity.

### Aims

2.1

Primary:

To characterize acute neural and autonomic regulation during brief mindfulness-based and relaxation-based interventions.To differentiate mindfulness and relaxation in terms of their underlying regulatory processes.

Secondary:

To examine brain–body coupling as a dynamic link between neural activity and autonomic rhythms.To examine autonomic coupling, particularly the coordination between cardiac and respiratory dynamics, across mindfulness, relaxation, and control conditions.To explore speech processing and brief speech production as psychotherapy-relevant extensions of the main paradigm.To identify psychological and lifestyle-related correlates of individual responsiveness.

### Research questions

2.2

Primary:

How do mindfulness-based and relaxation-based interventions differ in their acute neural, autonomic, and experiential effects?

Secondary:

How do neural dynamics relate over time to cardiac and respiratory regulation during stress, mindfulness, and relaxation?How are cardiac and respiratory dynamics coordinated across mindfulness, relaxation, and control conditions?When do subjective stress and relaxation ratings align with physiological and neural markers, and when do they diverge?Does temporal response functions (TRF)-based neural speech tracking and exploratory speech-production features differ across mindfulness, relaxation, and control conditionsWhich psychological and lifestyle characteristics are associated with stronger or weaker responsiveness to different interventions?

### Hypotheses

2.3

#### Primary

2.3.1

Preregistered hypotheses focus on differences between the conditions in (a) subjective stress and relaxation ratings, (b) HR, HRV (RMSSD), and respiration rate, and (c) global-band MEG power (theta, alpha, beta).

#### Secondary

2.3.2

TRF-based neural speech tracking is included as a preregistered stimulus-engagement measure: TRF-based speech tracking is expected to be stronger in the control/podcast condition than in the mindfulness/body scan and relaxation/safe place imagery conditions. This expectation is based on the rationale that the podcast condition primarily requires sustained engagement with externally presented speech, whereas the body scan and safe place imagery conditions use spoken guidance to support internally oriented regulatory processes such as interoceptive attention, bodily awareness, or mental imagery.

Brain–body coupling outcomes are treated as preregistered non-directional mechanistic outcomes, whereas autonomic coupling extensions, time-resolved coupling extensions, speech-production features, and psychological or lifestyle correlates are treated as exploratory unless explicitly specified otherwise in the preregistration.

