### Standardization and auditory conditions

3.6

All auditory recordings are presented using standardized voice characteristics to minimize variability unrelated to the experimental manipulation. The same speaker’s voice and recording quality are used across all conditions. All auditory stimuli are approximately equal in duration (10 min), presented as spoken audio, and matched in general recording format. They differ primarily in their regulatory content and instructions.

The intervention duration was set to approximately 10 min for both mindfulness and relaxation exercises to align with prior work on brief mind–body interventions and to remain feasible in the MEG environment. Single short-session mindfulness interventions have been shown to affect state mindfulness, perceived stress, attention, and affect, and recent evidence suggests that 10-min and 20-min mindfulness meditations may produce comparable improvements in state mindfulness, supporting the use of a 10-min format to assess short-term state effects while minimizing participant burden (Ueberholz and Fiocco, 2022; Palmer et al., 2023; Luberto et al., 2020).

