#### Control condition (podcast)

3.6.3

The control condition consists of a spoken informational podcast presented in a calm, conversational voice. The selected segment discusses a general-interest scientific topic and is intended to provide coherent spoken input without guiding participants toward mindfulness, relaxation, imagery, breathing, or emotional regulation. The podcast therefore serves as a non-regulatory auditory control condition rather than an intervention condition. The podcast condition is matched to the mindfulness body scan and relaxation guided imagery conditions in duration, auditory modality, and general speech characteristics, including continuous spoken language, similar pacing, and speaker characteristics, while differing specifically in the absence of explicit regulatory instructions. This allows speech-related neural responses to be assessed across conditions using comparable spoken input without an explicit mindfulness, imagery, breathing, or relaxation component. The control condition therefore accounts for non-specific effects associated with listening to spoken audio, including auditory stimulation, sustained attention, and language processing, while focusing the comparison on intervention-specific regulatory processes such as attentional focus, interoceptive awareness, or imagery-based modulation.

The use of structurally matched audio conditions as controls is consistent with experimental designs in mindfulness and relaxation research, where non-regulatory spoken material, such as documentary or general-interest content, is used to control for sensory and attentional engagement without inducing targeted regulation processes (Palmer et al., 2023; Vieth and von Stockhausen, 2022; Yang et al., 2022).

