#### Neural measures

3.7.2

Neural activity is recorded continuously using MEG to capture fast neural dynamics during the resting baseline and all auditory conditions following the stress induction. Neural outcomes include spectral power estimates in predefined frequency bands relevant to regulatory processes, including alpha (8–13 Hz), theta (4–7 Hz), and beta (13–30 Hz), summarized using predefined sensor-level summaries (e.g., global and region-of-interest averages). Exploratory analyses may additionally examine condition-related differences within predefined sensor- or source-level regions of interest (e.g., frontal/midline, temporal/auditory, parietal/posterior), depending on the specific analysis plan. In addition, TRF-based neural speech-tracking analyses will relate acoustic features of the auditory stimuli to MEG activity, providing an index of neural tracking of the spoken audio material.

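### The TRF speech-tracking contrast compares three different recordings, so unmeasured acoustic differences cannot be separated from the engagement that it is meant to index

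*Protocol article*

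**What the plan says.** Section 2.3.2 sets the direction of the contrast ("TRF-based speech tracking is expected to be stronger in the control/podcast condition than in the mindfulness/body scan and relaxation/safe place imagery conditions") and its meaning: "TRF-based neural speech tracking is included as a preregistered stimulus-engagement measure". The rationale given there and in section 1.6 is that the podcast holds attention on outside speech, while the two exercises turn it inward.

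Section 3.7.2 states the input to the measure: "TRF-based neural speech-tracking analyses will relate acoustic features of the auditory stimuli to MEG activity". The predictor in each condition is therefore that condition's own audio.

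On comparability, section 3.6 says of the three stimuli "They differ primarily in their regulatory content and instructions", and adds "The same speaker’s voice and recording quality are used across all conditions". Section 3.6.3 says the podcast is matched to the exercises in duration, modality and "general speech characteristics, including continuous spoken language, similar pacing, and speaker characteristics, while differing specifically in the absence of explicit regulatory instructions". It concludes: "This allows speech-related neural responses to be assessed across conditions using comparable spoken input".

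Section 3.9 models condition as a three-level within-subject factor, with condition order and medication status as example covariates. Section 4.3 lists artifacts, heterogeneity, recovery, habituation, fatigue and carryover as limitations. Stimulus acoustics is not among them.

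**The concern.** How well a temporal response function (TRF) predicts MEG depends on the listener and on the stimulus. With the neural response per unit of envelope held fixed, a recording with less speech or a flatter envelope drives less predictable signal and gives a lower prediction correlation.

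Each condition is described as a single stimulus: one numeric code per condition in section 3.3, one body scan, one safe place exercise and one podcast segment in sections 3.6.1 to 3.6.3. A condition difference in tracking is thus also a recording difference. Every participant hears the same three recordings, so an acoustic difference is a constant bias that neither order randomisation nor more participants will average out. The healthy cohort uses the identical paradigm (section 3.4.6), so its condition contrast carries the same confound.

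At stake is the interpretation of a preregistered directional hypothesis. A property of the audio could be reported as evidence that the exercises draw attention away from external speech. In the other direction, it could hide a true engagement difference.

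**Working it through.** The protocol gives no effect size, power or acoustic figure for this contrast, and N = 30 rests on feasibility (section 3.4.2.1). There is no stated figure to reproduce. The check asks how far acoustics alone can move the measure.

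**Inputs from the protocol:** about 10 min per condition; MEG resampled to 100 Hz; N = 30; two-sided alpha 0.05.

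**Assumed, because the protocol gives none:** pause shares, modulation depth, signal-to-noise level, podcast prediction r of 0.05 to 0.10, and SD of the within-person difference of 0.02 to 0.03.

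**Step 1. Simulation with identical neural gain and noise.** A ridge TRF was fitted with two-fold cross-validation, 12 runs per setting, and scored on the whole recording. Mean prediction r:

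| Setting | Lower signal-to-noise | Higher signal-to-noise |
|---|---|---|
| 10% pauses | 0.142 | 0.283 |
| 20% pauses | 0.130 | 0.263 |
| 30% pauses | 0.126 | 0.254 |
| 50% pauses | 0.102 | 0.215 |
| 10% pauses, modulation depth 0.8 | 0.118 | 0.222 |
| 10% pauses, modulation depth 1.2 | 0.167 | 0.321 |

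The first four rows have modulation depth 1.0.

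- 50% versus 20% pauses: 1 − 0.102/0.130 = 22% lower; 1 − 0.215/0.263 = 18% lower.
- 20% versus 10% pauses: 1 − 0.130/0.142 = 8% lower; 1 − 0.263/0.283 = 7% lower.
- Modulation depth 1.2 versus 1.0: 0.167/0.142 = 1.18 and 0.321/0.283 = 1.13, so 18% and 13% higher.

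A separate simulation with a known response kernel (no fitting, 30 runs) gave r = 0.081, 0.075 and 0.060 at 10%, 20% and 50% pauses. These are drops of about 7% (0.075/0.081) and 20% (0.060/0.075).

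**Step 2. Hand check.** For small r, r is roughly proportional to the square root of envelope power. If power scales with speech share, 20% versus 50% pauses gives √(0.50/0.80) = 0.79, or 21% lower, in line with Step 1. For 10% versus 20%, √(0.80/0.90) = 0.94, or 6% lower, close to the simulated 7–8%.

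**Step 3. Consequence at N = 30 with equal engagement.** Use r = √(SNR/(1 + SNR)), with SNR proportional to envelope power, and a two-sided paired t-test through the noncentral t distribution. Worked case: podcast r = 0.10 gives SNR = 0.01/0.99 = 0.0101. With 20% less power, SNR = 0.00808 and r = 0.0895, a difference of 0.0105. With SD 0.02 the noncentrality is (0.0105/0.02) × √30 ≈ 2.87, and the chance of significance is 0.79. With SD 0.03 it is 0.46.

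| Envelope power in guided audio | Chance of a significant difference |
|---|---|
| equal | 0.05 |
| 10% less | 0.07 to 0.27 |
| 20% less | 0.15 to 0.79 |
| 30% less | 0.30 to 0.99 |
| 50% less | 0.73 to about 1.00 |

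Ranges run over the assumed r and SD. These are single unadjusted comparisons; the family-wise correction in section 3.9.3 would lower them somewhat but would not remove the bias.

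**The case against.** The strongest reply is that the protocol already addresses comparability. Continuous speech and similar pacing bear directly on pauses and speech rate, and the same speaker and recording quality remove other differences. This stands as a narrowing of the problem: a 20% versus 50% pause split sits poorly with that description, and the 7–8% shift for 10% versus 20% may be nearer to what such matching leaves. But the match is stated in words, without a measured value or tolerance. The engagement reading needs more than similar pacing.

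Two stronger readings are tempting. A reader might infer that any acoustic difference favours the hypothesis. It does not: deeper modulation in the guided audio raises tracking there and works against the predicted direction. A reader might also infer that the body scan and imagery recordings contain longer silences because of what they ask of listeners. That is plausible, but sections 3.6.1 and 3.6.2 mention no silences and the audio cannot be inspected.

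It is also fair that scoring windows, null construction and training data are details that a condensed article may leave to the preregistration or analysis plan. Their absence here is not the fault. Both simulations score silence along with speech, which the protocol does not say it will do; speech-only scoring would shrink the pause part of the effect. The fault is the stated inference from a cross-recording contrast to engagement.

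Finally, the measure is secondary. Section 3.7.6 places it under exploratory speech analyses while also calling it preregistered, and section 4.4 limits findings to mechanistic and descriptive reading. This caps the importance of the point. It does not make the engagement reading identifiable.

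**Conclusion.** The concern holds as a problem of interpretation. Condition and recording are fully confounded for the TRF contrast, and the document gives no measured match that would let a difference be assigned to engagement. Acoustic differences could shift prediction r by about 7–8% (10% versus 20% pauses) to 18–22% (20% versus 50%) with identical neural gain, in a direction that depends on which recording carries more envelope power. At N = 30, a 10% deficit in envelope power matters modestly and a 30% deficit can matter a great deal. Every acoustic, r and SD value behind these figures is an assumption. The document does not show that the recordings differ, so it does not support a claim that the hypothesis will be falsely confirmed. Correction is worthwhile before results are read. The primary hypotheses in section 2.3.1 do not depend on it.

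**What to change.** 1. Measure and report pause share, speech rate and envelope variance for each of the three recordings.
2. Base the TRF contrast on speech-present segments matched, or adjusted, on these quantities, with equal training data per condition.
3. Express each participant's score relative to a null built from time-shifted envelopes of the same recording.
4. In section 2.3.2, make the engagement reading conditional: keep it only if the contrast survives the matching, and otherwise report a condition/stimulus difference.
5. Add stimulus acoustics to the limitations in section 4.3.

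If the preregistration already contains steps 1 to 3, a cross-reference is enough for those, and steps 4 and 5 remain.

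The cost is analysis time on audio and MEG data that the study will already hold, with no design change or extra participant burden. The downside is that some data per condition are dropped, so TRF estimates become slightly noisier.
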